### 9.3 Multivariate analysis

Multivariate analyses will be used to test relations between  $AUC_{0-24h}$  and the tobramycin dose corrected for bodyweight and potential other confounders.

## **10. ETHICAL CONSIDERATIONS**

### **10.1 Regulation statement**

This study will be conducted according to the principles of the Declaration of Helsinki (version 9, October 2008, [www.wma.net](http://www.wma.net)) and in accordance with the Medical Research Involving Human Subjects Act (WMO).

### **10.2 Recruitment and consent**

Participants will be recruited from the outpatient clinic of pulmonology. First, patients will be contacted by their physician. If patients are willing to participate, they are referred by their treating physician to the investigator. Their treating physician gives the intended participant the subject information brochure of this study. On day 1 of the contact between patient and investigator (see flow diagram page 15), in- and exclusion criteria will be checked, and the –study participants will be informed about the nature and goals of the study, as well as the advantages and disadvantages of study participation. Questions will be answered and sufficient time (2 weeks) will be offered. If participants so wish they will be offered the opportunity to see an independent physician. Both the participant and the investigator will sign the informed consent if the patient is willing to participate.

For the informed consent and the subject information letter see attachments.

### **10.3 Benefits and risks assessment, group relatedness**

No direct benefits to participants are expected. The risks are deemed relatively minor; there could be transient cough or dyspnea reactions immediately following inhalation.

### **10.4 Compensation for injury**

The UMCG has a liability insurance that is in accordance with article 7, subsection 6 of the WMO.

The UMCG (also) has an insurance which is in accordance with the legal requirements in the Netherlands (Article 7 WMO and the Measure regarding Compulsory Insurance for Clinical Research in Humans of 23th June 2003). This insurance provides cover for damage to research subjects through injury or death caused by the study.

1. € 450.000,-- (i.e. four hundred and fifty thousand Euro) for death or injury for each subject who participates in the Research;
2. € 3.500.000,-- (i.e. three million five hundred thousand Euro) for death or injury for all subjects who participate in the Research;

3. € 5.000.000,-- (i.e. five million Euro) for the total damage incurred by the organisation for all damage disclosed by scientific research for the Sponsor as 'verrichter' in the meaning of said Act in each year of insurance coverage.

The insurance applies to the damage that becomes apparent during the study or within 4 years after the end of the study.

### **10.5 Incentives**

Subjects whom participating the study after inclusion will receive 100 euro in gift certificates per visit. This applies only to the visits where the participant is inhaling the tobramycin. This amounts to the minimum wage of 8,38 Euro per hour. They will also receive meals during their visit in the hospital and their travel expenses. For the first visit, checking the in- and exclusion criteria and explanation of the study, the participant will receive 10 euro in gift certificates. For the second visit, signing the informed consent and undergo a medical check and perform a spirometry, they will receive 15 euro in gift certificates.

## **11. ADMINISTRATIVE ASPECTS, MONITORING AND PUBLICATION**

### **11.1 Handling and storage of data and documents**

Handling of the personal data in this observational study will comply with the Dutch Personal Data Protection Act. Data will be handled confidentially and anonymously. To trace the data of individual patients, the study will use a subject identification code list that is linked to the date of the participating patients. The code will not be based on the patient initials and birth date, but on number of enrolment into the study. At the end of the study, all data will be kept for of 20 years

### **11.2 Monitoring and Quality Assurance**

Not applicable

### **11.3 Amendments**

A 'substantial amendment' is defined as an amendment to the terms of the METC application, or to the protocol or any other supporting documentation, that is likely to affect to a significant degree:

- the safety or physical or mental integrity of the subjects of the trial;
- the scientific value of the trial;
- the conduct or management of the trial; or
- the quality or safety of any intervention used in the trial.

All substantial amendments will be notified to the METC and to the competent authority.

Non-substantial amendments will not be notified to the accredited METC and the competent authority, but will be recorded and filed by the sponsor.

### **11.4 Annual progress report**

As we expect to end this study within one year, the sponsor/investigator will submit a final report of the trial to the accredited METC after terminating the study. Information will be provided on the date of inclusion of the first subject, numbers of subjects included and numbers of subjects that have completed the trial, serious adverse events/ serious adverse reactions, other problems, and amendments.

### **11.5 End of study report**

The sponsor will notify the accredited METC and the competent authority of the end of the study within a period of 90 days. The end of the study is defined as the last patient's last visit.

In case the study is ended prematurely, the sponsor will notify the accredited METC and the competent authority within 15 days, including the reasons for the premature termination.

Within one year after the end of the study, the investigator/sponsor will submit a final study report with the results of the study, including any publications/abstracts of the study, to the accredited METC and the Competent Authority.

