**Table 2. Timetable of the study**

| Visit | Time table          | Time needed | Procedure                                                                                                                                                                                                                                                                                                        |
|-------|---------------------|-------------|------------------------------------------------------------------------------------------------------------------------------------------------------------------------------------------------------------------------------------------------------------------------------------------------------------------|
| 1     | Day 1               | 15 minutes  | Explanation study design and invitation to participate in the study                                                                                                                                                                                                                                              |
| 2     | Day 15              | 30 minutes  | Informed consent
Routine medical check, including spirometry and if necessary a X-ray of the chest                                                                                                                                                                                                            |
| 3     | Day                 | 13 hours    | Inhalation instruction
Medication inhalation, 1 st dose = 30 mg
Inhalation flow measurement
Collecting inhalation device
Measuring amount of tobramycin remaining in the device
Serum samples collection – from indwelling venous catheter
Spirometry
Scoring of adverse effects |
| 4     | Day 7 after visit 3 | 13 hours    | Inhalation instruction
Medication inhalation, 2nd dose = 60 mg
Inhalation flow measurement
Collecting inhalation device
Measuring amount of tobramycin remaining in the device
Serum samples collection – from indwelling venous catheter
Spirometry
Scoring of adverse effects             |

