| 5     | Day 7 after visit 4 | 13 hours    | Inhalation instruction
Medication inhalation, 3rd dose = 120 mg
Inhalation flow measurement
Collecting inhalation device
Measuring amount of tobramycin remaining in the device
Serum samples collection – from indwelling venous catheter
Spirometry
Scoring of adverse effects            |
| 6     | Day 7 after visit 5 | 13 hours    | Inhalation instruction
Medication inhalation, 4th dose = 240 mg
Inhalation flow measurement
Collecting inhalation device
Measuring amount of tobramycin remaining in the device
Serum samples collection – from indwelling venous catheter
Spirometry
Scoring of adverse effects            |

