## **7.6 Follow-up of subjects withdrawn from treatment**

Follow-up will be done by their chest physician or their general practitioner

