### **8.4 Follow-up of adverse events**

All AEs will be followed until they have abated, or until a stable situation has been reached. Depending on the event, follow up may require additional tests or medical procedures as indicated, and/or referral to the general physician or a medical specialist. SAEs need to be reported till end of study within the Netherlands, as defined in the protocol

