## 9. STATISTICAL ANALYSIS

### 9.1 Descriptive statistics

Descriptive statistics will be used for calculation (geometric) mean and (interquartile) range of observed age, weight, length, dose, clinical parameters, (unbound)  $AUC_{0-24h}$ , and  $C_{max}/MIC$  ratio, (unbound)  $AUC_{0-24h}/MIC$ ,  $T_{max}$ ,  $C_{max}$ ,  $T_{1/2}$  will be calculated with a 95% confidence interval. The other end-point will be proportions of subjects reporting adverse effects on all treatment days and / or percentage of drop of FEV1 of more than 10%.

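### No contact is planned after the 240 mg visit, so adverse events that start later have no planned capture after the highest dose, while each lower dose is followed by a visit a week later

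*Protocol*

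**What the plan says.** **Schedule.** In Table 2 the 30 mg dose is given at visit 3. The later dosing visits are timed as "Day 7 after visit 3" (60 mg), "Day 7 after visit 4" (120 mg) and "Day 7 after visit 5" (240 mg). Each lasts 13 hours and includes scoring of adverse effects. The last row is visit 6, "Medication inhalation, 4th dose = 240 mg". No later visit or call appears in Table 2 or elsewhere in the protocol.

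**End of study and SAE reporting.** Section 11.5: "The end of the study is defined as the last patient's last visit". Section 8.4: "SAEs need to be reported till end of study within the Netherlands". Section 8.4 also has adverse events followed up until they resolve or stabilise.

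**Withdrawn patients.** Section 7.6: "Follow-up will be done by their chest physician or their general practitioner". It does not say that new events found there come back to the study.

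**What is counted.**
- Section 7.1.1 names adverse events as part of local tolerability, without a time window.
- Section 8.2.1 records events occurring during the study, again without a window per dose.
- Section 7.3.7 measures FEV1 up to 90 minutes after inhalation, at every dose.
- Section 9.1 describes the adverse-effect endpoint: "The other end-point will be proportions of subjects reporting adverse effects on all treatment days".

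**The concern.** Tolerability is a primary objective beside pharmacokinetics (section 3). Section 6.6 explains that 240 mg is there to examine tolerability above the comparator device's dose. It is also more than the three earlier doses together (30 + 60 + 120 = 210 mg). Section 12.1 states that this product has not yet been studied clinically, and section 8.5 provides no safety board.

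The dose about which least is known is thus the one with no return visit. The follow-up rule in section 8.4 manages events that are already known and does not find new ones. If nothing is recorded in the days after 240 mg, a reader cannot tell whether nothing happened or nobody asked. The same applies to a patient who withdraws: planned study contact ends at the last dose that patient received, which may be the one that caused the withdrawal.

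**Working it through.** The protocol states no figure for an adverse-event window, so there is none to reproduce. The windows follow from Table 2 and sections 7.3.3, 7.3.7 and 9.1.

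**Step 1. Reach of planned contact after each dose**
- After 30, 60 and 120 mg, the next visit is 7 days later: 7 × 24 = 168 h.
- After 240 mg, contact ends with the last blood sample at 12 h (section 7.3.3) or with the 13-hour visit (Table 2).
- Ratio: 168 / 12 = 14.0, or 168 / 13 = 12.9.

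**Step 2. Which comparisons are affected**

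| Data | Window after 30, 60, 120 mg | Window after 240 mg | Equal? |
|---|---|---|---|
| FEV1 fall (7.3.7) | 90 min | 90 min | Yes |
| Adverse effects counted strictly on the treatment day (9.1) | dosing visit | dosing visit | Yes |
| All adverse events assigned to the preceding dose (data of 7.1.1, 8.2.1, 8.3) | up to 168 h | 12 to 13 h | No |

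Only the last row is unequal. The protocol does not say to which dose an event between visits belongs, or whether section 9.1 counts an event by its day of onset or by the day it is reported.

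**Step 3. How large the effect could be (illustration)**

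The protocol gives no adverse-event rate and no onset pattern. Assume a weekly risk w that is the same at every dose, with a constant hazard. The chance that one patient has an event within h hours is

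p = 1 − (1 − w)^(h/168).

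With w = 20% and h = 12: p = 1 − 0.8^(12/168) = 0.0158. Among 8 patients, the expected number affected is 8 × 0.20 = 1.6 after a lower dose and 8 × 0.0158 = 0.13 after 240 mg. The chance of seeing at least one is 1 − 0.8^8 = 83% against 1 − (1 − 0.0158)^8 = 12%.

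| Assumed weekly risk | Expected of 8, lower dose | Expected of 8, 240 mg (12 h) | Chance of at least one, lower dose | Chance of at least one, 240 mg (12 h) |
|---|---|---|---|---|
| 10% | 0.8 | 0.06 | 57% | 6% |
| 20% | 1.6 | 0.13 | 83% | 12% |
| 30% | 2.4 | 0.20 | 94% | 18% |
| 50% | 4.0 | 0.39 | over 99% | 33% |

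Taking 13 h instead of 12 h changes little: at 20% the chance at 240 mg is 13%. If every event starts within 12 h of inhalation, nothing is lost and the difference is zero.

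**Step 4. SAE reporting**

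Sections 8.4 and 11.5 together close SAE reporting at the last visit of the last patient. If that patient completes Table 2, this is the day of the 240 mg dose. For the other patients the study is still open for some time after their own visit 6, but no one is scheduled to ask them.

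**The case against.** A reader might infer that the dose comparison of tolerability as a whole is biased in favour of 240 mg. The documents do not support that, for these reasons:

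- **The endpoint windows are equal.** Section 9.1 ties the adverse-effect endpoint to treatment days, and FEV1 runs to 90 minutes at every dose. This stands. Neither measure is biased by the missing contact.
- **Seven days is visit spacing, not a stated observation window.** There is no diary and no call between visits, and recall after a week is imperfect. This stands: the lower doses have an opportunity to report, not full observation.
- **The direction is not fixed.** If events are counted on the day they are reported, an event in the week after 120 mg, mentioned at visit 6, could count on the 240 mg day. This stands. The under-count at 240 mg arises only when events go to the preceding dose.
- **The end of study is a date for the whole trial.** It coincides with visit 6 only for the last patient. For the others, an event reported spontaneously before that date still falls within the study. This stands, and it is why Table 2 carries the argument more than section 11.5 does.
- **The expected reactions are acute.** Sections 7.4.1 and 10.3 describe cough and dyspnoea tied closely to inhalation, and section 12.2 links kidney and ear toxicity to prolonged exposure. A reader could calculate that about 92% of events after 240 mg would be missed (1 − 13/168), but that needs onset spread evenly over the week, which nothing in the protocol supports.
- **The analysis is small and descriptive.** There are eight patients, and no test of adverse-event rates between doses is specified.

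These points remove the claim of a biased primary comparison. They leave the gap itself: no planned contact after the last dose, and unequal capture in the all-event data.

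**Conclusion.** The point holds as a gap in planned safety capture. Adverse events that start after the 240 mg visit, or after the last dose in a withdrawn patient, are not sought by any planned study contact. Each earlier dose is followed by a visit a week later at which they can be reported. For the last patient, SAE reporting also ends on the dosing day.

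The FEV1 endpoint and a strict treatment-day count are unaffected. A summary of all events that assigns each to the preceding dose would under-count at 240 mg, with planned contact about 13 to 14 times shorter. How many events that means cannot be determined from the protocol. It is none if all onsets fall within 12 hours, and the larger differences in the illustration rest on an assumed weekly risk and a constant hazard. This is a modest, inexpensive improvement and not a fault that invalidates the tolerability analysis.

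**What to change.** 1. **Table 2:** add a telephone safety contact 7 days after visit 6, and 7 days after the last dose for any withdrawn patient (also in section 7.6). Use the same adverse-event questions as at the visits, and record the date of onset.
2. **Section 11.5:** define the end of study as the last such contact, so that SAE reporting under section 8.4 covers it.
3. **Section 9.1:** report adverse events by dose in two separate windows, the treatment day and the 7 days after each dose, and state that an event between visits belongs to the preceding dose.

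No dose, dosing interval or treatment rule changes. The cost is about eight short calls, a few more if withdrawn patients are replaced, a wording amendment, and a study end one week later.

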### **11.6 Public disclosure and publication policy**

All investigators and sponsor are part of the UMCG and/or Rijksuniversiteit Groningen. They have agreed between them that results will be submitted for publication with joint authorship. The trial will be added in a public registry at [www.Clinicaltrials.gov](http://www.Clinicaltrials.gov).

## 12. STRUCTURED RISK ANALYSIS

### 12.1 Potential issues of concern

#### a. Level of knowledge about mechanism of action

Tobramycin is an antibiotic drug from the pharmacotherapeutic group of aminoglycoside antibacterials which are useful in infections caused by aerobic Gram-negative bacteria, including *P. aeruginosa*. It is derived from the aminoglycoside antibiotic complex nebramycin produced by a strain of *Streptomyces tenebrarius*.

The exact mechanism of action of aminoglycosides is not known. Binding to the bacterial 30S (also 50S) ribosomal subunit, inhibiting the translocation of the peptidyl-tRNA from the A-site to the P-site, as well as misreading of mRNA have been reported, which leaves the bacterium unable to synthesize proteins that are vital to its growth .

#### b. Previous exposure of human beings with the test product(s) and/or products with a similar biological mechanism

No clinical studies have been performed with DP tobramycin yet. However, various studies have described the pulmonary administration of tobramycin, both administered by nebulisation as by dry powder inhalation. The earliest studies were performed in the late 1980s and early 1990s. TOBI® nebulizer solution, Bramitob® nebulizer solution and TOBI® Podhaler® inhalation powder are all registered medicinal products indicated for the treatment of colonization and chronic infections of the lung by sensitive *P. aeruginosa* strains in CF patients aged 6 years and older. In patients with non-CF bronchiectasis *P. aeruginosa* colonization is associated with clinical deterioration and these patients are treated with inhaled tobramycin as well. In practice, the same posology is applied in non-CF bronchiectasis patients as in CF patients.

Several studies in the CF population with inhaled tobramycin were done in the late 1980s and early 1990s with promising results . However not all therapies that are effective in CF are effective in non-CF bronchiectasis .

Later, studies with tobramycin solution for inhalation were performed in patients with non-CF bronchiectasis. Barker et al. investigated 74 patients divided in two groups. 37 patients received 300 mg tobramycin solution via a nebulizer twice daily for 28 days, the others received placebo. The patients treated with tobramycin had a significant reduction in sputum *P. aeruginosa* density at all time points of the study. The placebo group had a negligible change in sputum density at all time points. Unfortunately, the incidence of dyspnoea, chest pain and wheezing was significantly greater in the tobramycin group.

Orriols et al. studied 17 patients with non-CF bronchiectasis colonized with *P. aeruginosa*, divided in two groups. Group A received both tobramycin and ceftazidim via nebulisation inhalation and group B was treated symptomatically. One patient of group A withdrew due to bronchospasm despite intense bronchodilator treatment. One patient of group B died due to respiratory failure after 300 days of follow up. No differences in lung function or arterial blood gas analysis were seen between the two groups. There was only one hospital admission in group A and seven patients of group B who had to be admitted. In both groups *P. aeruginosa* was still present. They did not study sputum density .

Couch et al. studied 74 patients with non-CF bronchiectasis colonized with *P. aeruginosa*. Patients were evenly divided in two groups, one group received tobramycin inhalation therapy and the other group received placebo. The treatment group received tobramycin for four weeks 300 mg twice daily. This group had a significant reduction in sputum *P. aeruginosa* density while the placebo group showed no change. The incidence of dyspnoea, wheezing and chest tightness was again significantly greater in the tobramycin group .

c. Can the primary or secondary mechanism be induced in animals and/or in ex-vivo human cell material?

No, the main study parameters/endpoints are AUC0-12 (area under the curve from 0 -12 h), Cmax (maximum plasma concentration), Tmax (time to maximum plasma concentration), Ka (absorption rate constant), T1/2 el (terminal elimination half-life), CL/F (clearance following pulmonary administration (F= bioavailability)). Furthermore, local tolerability of DP tobramycin will be determined by lung function measurement and questioning for adverse events. These data can only be obtained by a study in patients.

d. Selectivity of the mechanism to target tissue in animals and/or human beings

Preclinical safety studies performed with tobramycin are safety pharmacology, repeated dose toxicity, genotoxicity, and toxicity to reproduction studies. Renal toxicity and ototoxicity are the main hazards of tobramycin for humans. These toxicities are mainly seen when high systemic levels of tobramycin are reached and it is unlikely that these levels will be reached after pulmonary administration at the doses administered in this study. No increase in carcinogenicity or genotoxicity was found

e. Analysis of potential effect

Ramsey et al. investigated 600 mg tobramycin in total divided in t.i.d. This showed clinical effectiveness without serious adverse events. After this study the dose administered was compared with this dose .

Barker et al. investigated 74 patients divided in two groups. 37 patients received 300 mg tobramycin solution via a nebulizer twice daily for 28 days, the others received placebo. The patients treated with tobramycin had a significant reduction in sputum *P. aeruginosa* density at all time points of the study. The placebo group had a negligible change in sputum density at all time points. Unfortunately, the incidence of dyspnoea, chest pain and wheezing was significantly greater in the tobramycin group .

